### 2.9. Blinding

Outcome assessors and the data analyst will remain blinded to group allocation. Given the nature of the interventions, i.e., exercise and education sessions, blinding participants and therapists is not feasible. A password-protected emergency unmasking system will be established. Unblinding will be authorized only when strictly necessary for safety reasons to preserve trial integrity.

### 2.10. Interventions

Two active, therapist-guided telerehabilitation protocols will be combined with education and compared with usual care: (a) an MBE program, and (b) a low-intensity aerobic and strength training program. Usual care will reflect routine medical management. All sessions will be delivered live Via Microsoft Teams, with groups of ≤7–8 participants, once weekly for 12 consecutive weeks, consistent with previous research in ME/CFS and PCS [29,43]. Each session will last 45 min, increasing by 5 min each month. Exercises will require only a chair, with both seated and standing options available. Adjustments based on physical performance and perceived fatigue or dyspnea will follow pacing principles to minimize PEM risk. Therapists will guide participants using in-session ratings of perceived exertion (2–3/10) and simple cues to maintain a safe and comfortable exercise practice. Participants may also pause or re-join sessions as needed and will be encouraged to practice regularly using recorded materials. Attendance to ≥70% of the 12 scheduled sessions will be considered adequate exposure. A session will be considered attended if the participant joins the live class and takes part at least partially (≥15 min or completion of ≥1 exercise block), in line with pacing allowances. Attendance will be tracked Via Microsoft Teams and verified by therapist logs.

#### 2.10.1. MBE Group

This group will receive a therapeutic program combining health education (15 min) and MBE (30 min). Educational content will include self-management, pacing, activity–rest planning, basic theoretical framework about the conditions, and familiarization with mindfulness and awareness practices and their purported benefits. To enhance proprioceptive and interoceptive awareness, therapists will follow a brief checklist (posture, breath, body-scan, pacing, and cognitive reappraisal cues) at the beginning of each session. Body awareness will be reinforced through short post-session exercises (attention to bodily sensations; effort rating using sensations; perceived calm), and weekly home-practice using prerecorded materials. Specific content is provided in Supplementary File S2. The 30-min MBE practice will consist of structured sequences of breathwork, chair or standing-based mindful movement (yoga inspired), and guided body awareness and relaxation (e.g., Yoga Nidra). Content will rotate across three themes (whole body, upper limbs, and lower limbs) and repeated throughout 12 weeks. Posture lists and progressions follow standardized guidelines [44], and are described in Supplementary File S2. Participants will continue with their usual medical care.

#### 2.10.2. Aerobic/Strength Low-Intensity Exercise Group

This group will receive a program combining health education (15 min) and exercise (30 min). Educational content mirrors that of the MBE group but emphasizes the role of exercise in symptom management. Specific content is provided in Supplementary File S2. The exercise component includes low-intensity strengthening using body weight, gentle aerobic-functional drills, and cool-down and stretching. Typical activities involve joint mobility, multi-joint strengthening with short sets, and simple aerobic drills adapted for home practice, with a calm return-to-rest routine. Program details and progression guidelines are listed in Supplementary File S2. Participants will continue with their usual medical care.

#### 2.10.3. Control Group (Usual Care)

Control participants will continue their usual medical care during the 12-week period.

#### 2.10.4. Criteria for Discontinuing or Modifying Allocated Interventions

Participants may pause or modify sessions at any time according to pacing principles. Therapists may recommend temporary pauses or adjustments based on symptoms. No cross-over between study arms will be permitted. The principal investigator (PI) will decide on discontinuation if safety concerns arise. Withdrawals will be respected without requiring justification. Temporary interruptions due to intercurrent illness or symptom flare will be permitted, with resumption when appropriate. Enrollment in other clinical trials will not be allowed. Any relevant changes in medical treatment will be documented but will not necessarily lead to withdrawal unless recommended by a physician. In the event of AEs, participants will be offered an individual videocall to address causes and adjust the intervention accordingly. More specific details are included in Supplementary File S2.

#### 2.10.5. Strategies to Improve Adherence to Interventions

Adherence will be promoted through structured education, short home-practice videos, a moderated WhatsApp group for reminders and troubleshooting, and individualized autoregulation (pacing, and option to switch exercise version or position). The Welltory app will be used to log daily fatigue, discomfort, and PEM warnings. Entries are time-stamped, and symptom logs are aligned with HRV data for safety reviews.

#### 2.10.6. Provisions for Post-Trial Care

Both programs are low-intensity, self-paced, and adaptable, thus no serious AEs are expected. After study completion, control participants will be offered access to the recorded sessions and materials of either intervention program.

### 2.11. Outcomes

Data will be collected using Microsoft Forms and videoconference assessments. Participants will complete online questionnaires within a 2-week window at their own pace. The PI will monitor submissions for completeness, and plausibility/inconsistency issues. Implausible or inconsistent entries prompt participant queries. Corrections will be documented without overwriting original data. During this 2-week period, participants will attend a ~20-min videocall to assess HRV first and then functional performance in a standardized sequence: Modified Sit-and-Reach Test (MSRT), One-Leg Stand Test (OLST), and 60-s Sit-to-Stand Test (STS-60), to limit fatigue carry-over. Videocalls will be scheduled Monday–Thursday, 10:00–13:00 and 16:00–19:00 avoiding meals and sleep times. Rescheduling will be allowed during flares. This approach minimizes participant burden and reduces the risk that lengthy procedures may influence performance or clinical status.

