### 2.2. Study Setting

The study is decentralized and fully remote. A single coordinating center will oversee recruitment, randomization, intervention delivery, data management, and safety monitoring. No in-person visits will be required. 

The study team comprises two senior physiotherapists and certified yoga instructors with more than 10 years of experience in therapeutic yoga, one physiotherapist with over 5 years of experience in therapeutic exercise for chronic fatigue and complex pain, three researchers responsible for online assessments, and one statistician in charge of data analysis. To ensure consistency across evaluations and intervention delivery, preparatory training sessions will be conducted prior to recruitment.

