### 2.15. Oversight and Monitoring

The PI will oversee trial supervision, coordinate all project activities, monitor progress, and implement corrective actions as needed. The research team will serve as the coordinating center, ensuring adherence to the protocol and maintaining high-quality trial conduct. As no serious AEs are anticipated, no independent data monitoring committee will be established. The PI will be responsible for ensuring trial safety and integrity, and will fully cooperate with any auditing procedures, providing all requested documentation. In the event of a major AE, the PI will promptly contact the participant’s treating physician and the Institutional Ethics Committee to determine the appropriate course of action.

Although no major protocol modifications are expected, any amendments will be first submitted to and approved by the Institutional Ethics Committee before implementation. Participants will be informed of any changes affecting their involvement, and updated study materials (e.g., information sheets) will be provided when necessary.

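### Plausibility review of the questionnaires, including the primary CFQ-14, is assigned to the PI, a role not listed as blinded; post-randomisation review should be masked or automated

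*Protocol article*

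**What the plan says.** Four parts of the protocol article bear on this.

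- **Data review (section 2.11).** "The PI will monitor submissions for completeness, and plausibility/inconsistency issues". The text continues: "Implausible or inconsistent entries prompt participant queries", and then: "Corrections will be documented without overwriting original data". These sentences cover the online questionnaires as a group. The CFQ-14, whose 12-week total is the primary outcome (section 2.11.1), is one of them.
- **Blinding (section 2.9).** "Outcome assessors and the data analyst will remain blinded to group allocation". The same section says that "blinding participants and therapists is not feasible". The PI appears in neither statement.
- **The PI's other duties (sections 2.10.4 and 2.15).** "The principal investigator (PI) will decide on discontinuation if safety concerns arise". Also: "The PI will oversee trial supervision, coordinate all project activities, monitor progress, and implement corrective actions as needed". Section 2.15 further makes the PI responsible for safety and sets up no independent data monitoring committee.
- **Staff available (sections 2.2 and 2.12).** The team includes "three researchers responsible for online assessments", and an assessor is to be on hand for questions when the questionnaire links go out.

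**The concern.** The primary outcome is a subjective self-report from participants who know their arm. If the person who decides which answers look odd also knows the arm, queries can be raised more readily in one arm than in another, without any intent to do so. A participant who receives a query may then change the answer. The result would be measurement error that differs by arm, entering after randomisation.

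Two features make this worth attention. The protocol expects a particular direction: section 1 hypothesises greater CFQ-14 improvement with MBE, and section 2.7 uses a one-tailed calculation for that reason. In addition, section 2.11 lets inconsistency, as well as implausibility, trigger a query. Inconsistency between items, visits or scales is a matter of judgement in a way that an out-of-range value is not.

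**Working it through.** **Who does what**

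| Role | Stated as blinded (2.9) | Stated as not blindable (2.9) | Reviews questionnaire entries (2.11) |
|---|---|---|---|
| Outcome assessors | yes | no | not stated |
| Data analyst | yes | no | not stated |
| Participants, therapists | no | yes | no |
| PI | no | no | yes |

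Review of the primary outcome data thus falls to the one role in the table whose masking the article leaves open. Deciding on discontinuation, answering for safety and coordinating all activities are hard to do without learning the arm. This is an inference from duties and not a statement in the text.

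**When it matters.** Under section 2.8, envelopes are opened only after baseline assessments are complete. The concern therefore applies to the 12-week and 3-month questionnaires.

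**The plan's planning figures, used below as a yardstick.** Section 2.7 gives a difference of 6, variance 56.5 (SD = √56.5 = 7.52), one-tailed α 0.05, power 80%, design effect 2 and dropout 20%.

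- Per arm: 2 × (1.645 + 0.842)² × 56.5 / 6² = 19.41
- With the design effect: 19.41 × 2 = 38.81
- With dropout: 38.81 / 0.80 = 48.5, rounded up to 49; 3 × 49 = 147

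This reproduces the stated sample size, which the present point does not affect.

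**Illustrative size.** The article gives no query or correction rate, so the inputs here are assumptions. If a fraction f of one arm's CFQ-14 totals is shifted by k points in one direction because of queries not made in the other arm, the bias in the mean difference is f × k.

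| f | k (points) | Bias (points) | Share of the 6-point difference |
|---|---|---|---|
| 5% | 1 | 0.05 | 0.8% |
| 5% | 3 | 0.15 | 2.5% |
| 10% | 3 | 0.30 | 5% |
| 20% | 3 | 0.60 | 10% |

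A harsher assumption, 15% shifted by 5 points, gives 0.75 points: 12.5% of the planning difference, or 0.75 / 7.52 ≈ 0.1 SD. With items scored 0 to 3, a 5-point shift needs at least two items changed per affected participant.

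**Effect on the error rate.** Take 39 completers per arm (49 × 0.80 = 39.2) and an unadjusted comparison of two arms. The standard error is 7.52 × √(2/39) = 1.70. A nominal two-sided 5% error becomes about 5.1% for a bias of 0.15, 5.4% for 0.30 and 6.4% for 0.60.

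**The case against.** The strongest reply is that most of the harm has to be inferred.

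- **Knowledge of allocation.** A reader might infer that the PI is unblinded. The article does not say so; section 2.9 lists the PI neither as blinded nor as unblindable, and it describes a protected unmasking system without saying whether that binds the PI. What stands is that masking during data review is not stated and that the PI's duties make knowledge of the arm likely.
- **Changing answers.** A reader might infer that the PI can alter scores or press participants to reconsider valid answers. The text supports neither. The query sentence names no issuer, changes are documented, and the original entry survives.
- **Scope on this scale.** The CFQ-14 has 14 items with four fixed options, so no single answer is out of range, and the review sentence is generic. This makes the risk smaller. It does not remove it, because patterns across items or visits can still be called inconsistent.
- **The trial's blinding as a whole.** A reader might infer that this undoes the single-blind claim. It does not. Blinding of the analyst, and of the assessors for heart rate variability and functional tests, is untouched. Assessor blinding never protected a self-report from unblinded participants, and the Discussion already acknowledges expectation and recall bias.
- **Detail left to other documents.** Query rules and the choice between original and corrected values often sit in a data management or analysis plan, so their absence from a condensed article is no fault. The assignment of the review to the PI, however, is stated in the article, and it is this assignment that can be improved.

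**Conclusion.** The point holds as a low-cost improvement of modest weight. The article gives post-randomisation plausibility review of the primary outcome to a role not listed as blinded, whose other duties make knowledge of allocation likely. Queries could therefore be selective by arm.

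The risk is small, because originals are retained and the CFQ-14 offers few entries to question. Its size cannot be estimated from the article. The illustrated biases, up to 0.60 points or 0.75 in the harsher case, rest wholly on assumed rates and on all shifts going one way. The point does not establish that the PI knows allocation or that the trial's blinding fails.

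**What to change.** - Assign completeness and plausibility review after randomisation to the blinded assessors already on the team. Alternatively, build required fields and fixed checks into the online form and apply them identically to all arms, so that no individual judgement is involved.
- Limit CFQ-14 queries to missing or technically impossible entries.
- Report the number of queries and corrections by arm, and add a sensitivity analysis comparing original with corrected values. Because originals are kept, this also covers any follow-up data already reviewed by the PI.

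The cost is slightly more work for the assessors, or a one-time change to the form, plus a short addition to the analysis plan. No new staff are needed. Running the original-versus-corrected comparison as a sensitivity analysis avoids forcing entry errors that participants have confirmed into the primary data set.

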#### 2.11.1. Primary Outcome

The primary outcome is the total score of the CFQ-14 (Spanish version) at 12 weeks (post-intervention). The CFQ-14 measures perceived physical and mental fatigue over previous weeks on a 4-point Likert scale (0 = “never”, 1 = “sometimes”, 2 = “often”, 3 = “always”), total score 0 to 42, with higher scores denoting greater fatigue. The Spanish version of the CFQ-14 has demonstrated adequate reliability and validity [45]. 

#### 2.11.2. Secondary Outcomes

Secondary outcomes include physiological, psychosocial, and functional performance measures.

Resting heart rate (HR) and HRV will be assessed using the Welltory mobile app (V4.16.100, Welltory Technologies Inc., Redwood City, CA, USA). Resting HR values will be obtained via photoplethysmography through the smartphone camera, while the time-domain HRV indices will be derived as proxies of autonomic balance. Previous studies report excellent agreement to estimate resting HRV using this method when compared with established referenced tools, including electrocardiography and medical-grade HR monitors (intraclass correlation coefficient > 0.90) [46]. Measurements will be made at the start of the video call. Participants will be instructed to sit quietly, breathe spontaneously, rest their forearms on their thighs, and hold the smartphone in their dominant hand, placing the index finger on the camera as indicated by the app. Speaking or moving during the recording will not be permitted. The 300-beat setting will be used to maximize precision. Both resting HR and HRV will be extracted from the same measurement.

Health-related quality of life will be evaluated with the 36-Item Short Form Health Survey (SF-36). This tool comprises eight domain scores (physical functioning, role-physical, bodily pain, general health, vitality, social functioning, role-emotional, mental health), each transformed into a 0–100 scale (higher scores indicate better health). Physical and mental component summary scores will also be calculated. The Spanish version of the SF-36 exhibits high internal consistency across domains [47]. The severity of anxiety and depressive symptoms will be assessed using the Hospital Anxiety and Depression Scale (HADS; Spanish version). The tool includes 14 items forming two 7-item subscales (from 0 to 21 points each). Scores ≥ 8 indicate clinically relevant symptoms. The Spanish version of the HADS is reliable and widely used in clinical and research settings [48]. Sleep quality will be assessed using the Spanish version of the Pittsburgh Sleep Quality Index (PSQI). The PSQI includes 19 items grouped in 7 components, namely, subjective quality, latency, duration, habitual efficiency, disturbances, medication use, daytime dysfunction, each scored from 0 to 3. The global score ranges from 0 to 21, with values >5 indicating clinically significant sleep problems. The Spanish version of the PSQI shows good validity and internal consistency [49].

Remote assessment of functional performance has been shown to be both feasible and reliable when delivered under standardized protocols and real-time supervision [50]. The study will follow international recommendations for remote physical performance testing [50]. Before assessment, participants will receive clear instructions to prepare a well-lit space and position the camera to provide a full-body lateral view. Each test will be demonstrated in advance, and corrective feedback will be provided as needed to ensure proper execution. 

Posterior chain flexibility will be measured using the MSRT. Participants will sit on a firm surface (e.g., floor) with legs extended, ankles neutral, and a one-fist gap between the knees. A small object (≤3–4 cm diameter) will be placed between the legs near the pelvis, aligned with the midline. With arms extended, participants will slide the object forward along the midline as far as possible while keeping knees extended and avoiding bouncing. The assessor will view from the side to ensure correct execution. Using a tape measure, the distance will be recorded in centimeters from the pubic symphysis (over clothing) to the nearest edge of the object at the farthest reach. Testing will stop immediately if pain or cramping occurs. Higher values indicate greater flexibility. Static balance will be assessed using the OLST. Participants will stand unaided on one leg with arms crossed over the chest, while keeping the contralateral leg off the ground. The maximum time (in seconds) that balance is maintained will be recorded, with the best performance of three consecutive attempts used for analysis. Lower-limb strength and endurance will be evaluated with the STS-60. Participants will perform repeated sit-to-stand movements from a standard armless chair for 60 s, with arms crossed over the chest. Effort will be self-regulated to a perceived exertion of approximately 6/10 (moderate). Participants will be instructed to maintain a comfortable pace and may slow down or pause if symptoms increase. The total number of valid repetitions (full stand and controlled sit) will be recorded.

#### 2.11.3. Other Secondary Measures

The Brief Pain Inventory (BPI; Spanish version) will be used to record pain intensity and interference. The BPI comprises 9 items addressing pain intensity and the degree to which pain interferes with daily activities such as sleep, mood, and work. Items are rated from 0 to 10, with higher scores indicating greater pain or interference. The Spanish version of the BPI demonstrates robust validity and reliability [51]. Interoceptive awareness and changes in body awareness will be measured using the Multidimensional Assessment of Interoceptive Awareness (MAIA) scale. This tool includes 23 items rated from 0 (never) to 5 (always) across eight domains (e.g., noticing, emotional regulation Via bodily sensations, interoceptive trust). Higher scores reflect greater interoceptive awareness [52]. Finally, pain-related fear and somatic vigilance will be evaluated using the Tampa Scale for Kinesiophobia (TSK; Spanish version) and the Anxiety Sensitivity Index (ASI; Spanish version). The TSK includes 17 items rated from 1 to 4, with higher scores indicating greater fear of movement [53]. The ASI consists of 16 items (total score: 0–64) assessing fear of anxiety-related bodily sensations, with higher scores denoting greater sensitivity [54].

#### 2.11.4. Adherence and Adverse Events

Adherence and AEs will be monitored using a digital daily diary (Microsoft Forms). Participants will record their completion of prescribed practice sessions, perceived exercise-related sensations, and any AEs or post-exertional symptom exacerbations. The diary will also capture health-relevant events, including menstruation (for women of reproductive age), intercurrent infections or reinfections, and recent vaccinations. A short free-text field will allow participants to note other relevant information (e.g., medication changes, acute stressors). All entries will be used to inform safety reviews and sensitivity analyses.

### 2.12. Data Collection, Retention, and Management

Only health-related data relevant to the study will be collected. For sociodemographic, clinical, and questionnaire-based data collection, links to Microsoft Forms will be sent to participants on the scheduled day, and an assessor will be available to address questions. Several engagement strategies will be implemented to maximize retention and reduce dropout, including providing clear and comprehensive information about the trial, maintaining direct communication with the research team through WhatsApp groups to foster trust and feedback, and sending regular reminders of upcoming sessions, diary completion, and follow-up assessments.

Personal information will be pseudonymized using unique alphanumeric codes for each participant. The file linking codes to participant identities will be securely stored in an encrypted, password-protected document on the institutional cloud server (Microsoft OneDrive), with access restricted to authorized data managers. All study data will remain within the institutional secure cloud environment, ensuring confidentiality, compliance with data protection policies, and safe collaborative work among the research team.

